# Comparison of three regimens with inhalational methoxyflurane versus intranasal fentanyl versus intravenous morphine in pre-hospital acute pain management: study protocol for a randomized controlled trial (PreMeFen)

**DOI:** 10.1186/s13063-023-07590-9

**Published:** 2023-09-05

**Keywords:** Analgesia, Pre-hospital, Emergency medicine, Acute pain, Opioids, Methoxyflurane

## Abstract

**Background:**

Pre-hospital pain management has traditionally been performed with intravenous (IV) morphine, but oligoanalgesia remain a recognized problem. Pain reduction is essential for patient satisfaction and is regarded as a measure of successful treatment. We aim to establish whether non-invasive methods such as inhalation of methoxyflurane is non-inferior to intranasal fentanyl or non-inferior to the well-known IV morphine in the pre-hospital treatment of acute pain.

**Method/design:**

The PreMeFen study is a phase three, three-armed, randomized, controlled, non-inferiority trial to compare three regimens of analgesics: inhalation of methoxyflurane and intranasal (IN) fentanyl versus IV morphine. It is an open-label trial with a 1:1:1 randomization to the three treatment groups. The primary endpoint is the change in pain numeric rating scale (NRS) (0–10) from baseline to 10 min after start of investigational medicinal product administration (IMP). The non-inferiority margin was set to 1.3, and a sample size of 270 patients per protocol (90 in each treatment arm) will detect this difference with 90% power.

**Discussion:**

We chose a study design with comparison of analgesic regimens rather than fixed doses because of the substantial differences in drug characteristics and for the results to be relevant to inform policymakers in the pre-hospital setting. We recognize that easier administration of analgesics will lead to better pain management for many patients if the regimens are as good as the existing, and hence, we chose a non-inferiority design. The primary endpoint, the change in pain (NRS) after 10 min, is set to address the immediate need of pain reduction for patients with acute prehospital pain. On a later stage, more analgesic methods are often available.

**Summary:**

PreMeFen is a non-inferiority randomized controlled trial comparing three analgesic regimens aiming to establish whether inhalation of methoxyflurane or intranasal fentanyl is as good as IV morphine for fast reduction of acute pain in the prehospital setting.

**Supplementary Information:**

The online version contains supplementary material available at 10.1186/s13063-023-07590-9.

## Background

Pre-hospital underuse of analgesics (oligoanalgesia) remains a global health problem [1–4]. Between 35 and 53% of patients describe moderate to severe pain during pre-hospital management [5], and pain management is considered a primary task for emergency medical service (EMS) providers [6, 7]. Still, barriers to adequate analgesia include challenging environment, lack of competence, and experience [8]. Although pre-hospital pain management often involves IV opioid administration [9], cannulation has been described to fail in 12–26% of adults [10], leading to a potential delay in administration of analgesia. Patients may benefit from a more easy-to-administer analgetic, which should be delivered safely, effectively, non-invasively and should be fast-acting. Reviews suggest two such alternatives: IN fentanyl, a synthetic opioid [8], and inhaled low-dose methoxyflurane, a volatile anesthetic from a group of fluorinated hydrocarbons [11]. Methoxyflurane in low dose is a non-narcotic analgesic widely used in Australia and New Zealand [11]. The slightly volatile gas is administered as a liquid via an inhalation chamber in a whistle-like pipe, while the exhaled air is filtered in a coal chamber on the same whistle [12].

## Study rationale

The rationale of the PreMeFen-study is to provide evidence for earlier, safe, non-invasive pain management in the pre-hospital setting.

We aim to investigate whether regimens of:Inhaled low-dose methoxyflurane is non-inferior to IN fentanyl orInhaled low-dose methoxyflurane is non-inferior to IV morphine orIN fentanyl is non-inferior to IV morphine

in managing a variety of moderate to severe acute pain conditions in adult patients from 18 years of age administered by the EMS.

## Study setting

Norway has a governmentally funded healthcare system aiming to provide equal access to healthcare regardless of geographical location and resource availability. The Ministry of Health and Care Services carries supervisory responsibility for all the public hospitals and is the owner of four regional health trusts [13]. The ambulance services are integrated in Norwegian specialist health service system [14–16]. This study will be conducted at the Innlandet Hospital Trust, Pre-Hospital Division (Norway), ground ambulances service. The service runs 44 ambulances with a catchment area of approximately 52,000 square kilometers and 360,000 inhabitants in rural and urban areas. Three ambulance stations were selected to include patients, of which two are based in cities (Gjøvik and Lillehammer), whereas one is rural (Gran). Selection was based on activity data to ensure adequate subject recruitment. The emergency medical communication center (EMCC) manages emergency medical calls from the public. EMCC is staffed with trained health care personnel (paramedics and nurses) using Norwegian Index for Emergency Medical Assistance (INDEX), a criteria-based medical dispatch guideline [17].

## Methods

### Study design

We applied the Norwegian Clinical Research Infrastructure Network (NorCRIN) templates [18] to design a randomized, controlled, open-label, three-arm, non-inferiority, phase three drug trial. The trial will be performed according to the principles of the Helsinki Declaration. The randomization is 1:1:1 to the three treatment groups, with 90 patients in each group, totaling 270 patients. Patients in all treatment groups follow a treatment regime rather than receiving a single drug dose. For ethical reasons, a placebo arm was excluded. The study protocol was drafted in accordance with the Standard Protocol Items: Recommendations for Interventional Trial guidelines (SPIRIT) [19].

### Allocation and randomization

The study kit contains all three IMP, patient information letter, information letter to receiving hospital, and a sealed randomization envelope. Computer-generated block randomization with variable block sizes is provided by the department of clinical trial unit (CTU), Oslo University Hospital. All the sealed randomization envelopes were provided in one batch from the CTU, which also kept the code file secret and hidden from the study team. The sealed envelopes were further distributed into the study kits by the study team. Following routine clinical primary survey, the EMS providers screen for eligibility and ask for consent. The study kit remains sealed until the patient is included, and the consent form is signed by the EMS provider. Patients are then randomized 1:1:1 between the three treatment regimes, as shown in Fig. 1.

**Fig. 1 Fig1:**
[figure not shown]
Flow chart study intervention

### Blinding

General blinding was considered unfeasible due to the complexity of study context, but the datasets is blinded for the statistician.

### Eligibility criteria

EMCC does not pre-screen patients, making eligibility evaluation solely to be performed on-scene. Patients considered not eligible are treated according to local analgesic protocols. See Table 1 for inclusion and exclusion criteria.

**Table 1 Tab1:** Inclusion and exclusion criteria

Inclusion criteria	Exclusion criteria
> 18 years of age	Life-threatening or limb-threatening condition requiring immediate management
Acute moderate to severe pain (both medical and traumatic etiology) defined by self-reporting pain ≥ 4 on numeric rating scale	Pregnancy or breastfeeding
Capable of giving informed consent	Know allergies, hypersensitivity, or serious side effects to opioids or methoxyflurane or other excipients
Normal physiology	Head injury or medical conditions with neurological impairment (Glasgow coma scale < 14)
	Previous malignant hyperthermia or persons with suspect genetic predisposition for malignant hyperthermia
	Massive facial trauma, visible nasal blockage, or on-going nose bleeding
	History of severe liver disease with jaundice and scleral icterus
	Dialysis or history of severe renal disease (known chronic kidney failure stage 4 or 5)
	Monoaminoxidase inhibitors last 14 days (pharmacological treatment of depression, Morbus Parkinson or narcolepsy)
	Myasthenia gravis
	Use of investigational medicinal product analgesics 12 h prior to inclusion
	Any condition that in the view of the study worker would suggest that the patient is unable to comply with study protocol and procedures

### Interventions

The intervention is the administration of IMP with three different medication regimens of inhalational methoxyflurane, IN fentanyl, and IV morphine; see Table 2. The schedule of activities is outlined in Table 3. After inclusion, baseline clinical data is obtained. Clinical data consists of NRS, Glasgow coma scale (GCS) [20], heart rate, blood pressure, oxygen saturation, and respiratory rate. IMP is given at T0. NRS is repeated after 5 min. All clinical data is repeated after 10, 20, and 30 min and upon arrival in emergency department, whatever comes first. The patient may receive additional doses of IMP from 5 min after first dose. The study duration is from ambulance scene arrival to patient handover in the emergency department (ED).

**Table 2 Tab2:** Medication regimens

IMP	Methoxyflurane	IN fentanyl	IV morphine
Dose	3 ml inhalation	18–70 years: 100 μg > 70 years: 50 μg	18–70 years: 0.1 mg/kg > 70 years or fragile: 0.05 mg/kg
Dose repetition	Yes, if needed	Yes, if needed interval 5 min	Yes, if needed interval 5 min
Maximum total dose	6 ml	500 μg	0.5 mg/kg

*IN* Intranasal, *IV* Intravenous, *IMP* Investigational medicinal product

**Table 3 Tab3:** Schedule of activities

Timepoint	T(x)	T_0_	T_5_	T_10_	T_20_	T_30_	T_ED_	Within 14 days
Description	Scene arrival	IMP adm	5 min	10 min	20 min	30 min	Arrival ED	
Inclusion and exclusion criteria	X							
Informed oral consent	X							
Physical examination including estimation of weight	X							
Medical history	X							
Allocation	X							
ECG (If chest pain)	(X)						(X)	
Intravenous access attempts	X							
Start administration of IMP		X						
SpO_2_	X			X	X	X	X	
Blood pressure	X			X		X	X	
Heart rate	X			X	X	X	X	
Respiration rate	X			X		X	X	
NRS	X		X	Primary endpoint	X	X	X	
GCS	X			X		X	X	
Patient satisfaction Likert scale							X	
HCP satisfaction Likert scale							X	
Troponin I/T							X	
Recording final diagnosis								X

*IMP* Investigational medicinal product, *ECG* Electrocardiogram, *SpO*_*2*_ Oxygen saturation, *NRS* Numeric rating scale, *GCS* Glasgow come scale, *HCP* Health care personnel

### Medication regimens

Administration of each of the 3 IMPs is based on pre-specified treatment regimens, including a flexible dosing of the analgesic and titration to effect, but only using the specific drug in the allocated treatment arm. Each regimen is defined with doses, dose intervals, and maximum doses (see Table 2 for medication regimes).

### Rescue medication

In cases where IMP fail to provide sufficient analgesic effect (NRS < 4) despite repeated doses, patients are treated with standard pain relief protocol. All analgesics other than the allocated IMP is referred to as rescue medication. Any need for rescue medication is noted with time and dose.

In cases where rescue medication is administered before the primary endpoint assessment at 10 min, the patient will be excluded from the per-protocol analysis.

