**Fig. 2 Fig2:**
[figure not shown]
Non-inferiority chart. The lines A–D represent mean and confidence interval of the differences in NRS-changes in the two treatment groups a and b. Examples A and B show that the agent a is inferior to agent b, while examples C and D confirm that agent a is non-inferior to agent b. IMP, investigational medicinal product; NRS, numeric rating scale

$${H}_{1}\to {H}_{2}\to {H}_{3}$$

The statistical chain of testing and decisions will be:*Test *$${H}_{1}$$*:* If part of the 95% confidence interval is below non-inferiority margin, we stop testing without any conclusion on efficacy. If the 95% confidence interval is above the non-inferiority margin, then we claim non-inferiority of methoxyflurane vs fentanyl and proceed with testing $${H}_{2}$$.*Test *$${H}_{2}$$*:* If part of the 95% confidence interval is below the non-inferiority margin, we stop testing without any further conclusion on efficacy. If the 95% confidence interval is above the non-inferiority margin, then we claim non-inferiority of methoxyflurane vs morphine and proceed with testing $${H}_{3}$$.*Test *$${H}_{3}$$*:* If part of the 95% confidence interval is below the non-inferiority margin, we stop testing without any further conclusion on efficacy. If the 95% confidence interval is above the non-inferiority margin, then we claim non-inferiority of fentanyl vs morphine.

The nominal significance level is set to 5%, and the non-inferiority margin is set to 1.3. Non-inferiority is determined based on a 1-sided equivalence *t*-test on the per protocol population and confirmed, for sensitivity reasons, on the modified intention to treat population.

We plan to compare the incidence of serious and non-serious adverse events between the groups using a chi-squared test or a Fisher exact test if necessary (expected frequency less than 5). We will summarize patient satisfaction and medical personnel view on practicality.

Demographic and baseline information of the three study groups will be compared using *t*-tests (means), Mann–Whitney *U* (medians), and chi-square (proportions) tests. If there are any significant differences, linear regression will be performed to adjust for significantly different covariates. No interim analysis will be performed.

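### Excluding patients rescued before 10 minutes from the per-protocol set makes the deciding analysis depend on treatment failure, and can favour non-inferiority when early rescue is commoner in the test arm

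*Protocol article*

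**What the plan says.** In the Rescue medication section, rescue follows failure of the allocated drug: "In cases where IMP fail to provide sufficient analgesic effect (NRS < 4) despite repeated doses, patients are treated with standard pain relief protocol". The definition is broad: "All analgesics other than the allocated IMP is referred to as rescue medication". The exclusion comes next: "In cases where rescue medication is administered before the primary endpoint assessment at 10 min, the patient will be excluded from the per-protocol analysis".

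The Statistics section determines non-inferiority "on the per protocol population and confirmed, for sensitivity reasons, on the modified intention to treat population". It sets out the fixed sequence H1, H2, H3 step by step. It does not name the population that governs each step, or say what follows if the two populations disagree. On error rate and margin it says: "The nominal significance level is set to 5%, and the non-inferiority margin is set to 1.3".

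Table 4 lists need for analgesia outside the allocated regimen as a secondary endpoint. The Discussion says that the trial compares regimens, meaning titration to effect with the allocated drug only.

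**The concern.** Needing another drug within 10 minutes is a failure of a regimen defined as titration with the allocated drug alone. The exclusion removes those failures from the analysis that decides the trial. It acts after randomisation and depends on how the patient is doing, so the two arms compared are no longer the randomised ones.

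A per-protocol analysis is often taken as the cautious choice for non-inferiority. That argument fails when the excluded patients are treatment failures. The case that matters is a test regimen that is worse by the full margin. More of its patients will then do badly, more will be rescued under the same rule, and their removal raises its mean by more than the comparator's. The trial is open-label, and the Limitations section accepts that the method of administration may influence the preferences of patients or providers, so rescue thresholds could also differ by arm. At stake is a false claim of non-inferiority, which in a fixed sequence also opens the next test.

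**Working it through.** **Inputs from the article.** Margin 1.3, read as −1.3 for the difference in mean reduction (test minus comparator); SD 2.20; 90 per arm; non-inferiority if the 95% CI lies wholly above the margin, a one-sided error of 2.5%; expected reductions 3.77 (methoxyflurane), 2.54 (fentanyl) and 2.70 (morphine).

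**Not in the article.** The share rescued before T10, and the effect of rescue on the T10 score. Both are assumed below.

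**The plan's own figure.** The Sample size section gives 88 per arm. The usual formula, n = 2(SD × (1.96 + 1.28)/Δ)², gives 61 for Δ = 1.3 (no true difference) and 79 for Δ = 1.3 − 0.16 = 1.14 (the difference expected for H3). The 88 is not reproduced, but it exceeds both, and nothing below depends on it.

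**Standard error.** 2.20 × √(2/90) = 0.328. A bias b toward non-inferiority gives a false non-inferiority rate at the margin of about 1 − Φ(1.96 − b/0.328).

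**Case 1: early rescue in the test arm only, worst responders removed.** Removing the lowest share q of a normal distribution raises the mean by SD × φ(z_q)/(1 − q).

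| Rescued, test arm | Shift (NRS) | Share of margin | False non-inferiority (simulated) |
|---|---|---|---|
| 2% | 0.11 | 8% | 5.0% |
| 5% | 0.24 | 18% | 11% |
| 10% | 0.43 | 33% | 27% |

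Check at 5%: 0.24/0.328 = 0.73, and 1 − Φ(1.23) = 11%.

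**Case 2: one rescue rule in both arms.** The true means are 1.40 (test) and 2.70 (comparator), a difference of −1.3. Patients whose pain would worsen by T10 without rescue (reduction below 0) are rescued with probability 0.10, 0.25 or 0.50.

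| Rescued, test / comparator | Per-protocol difference | False non-inferiority |
|---|---|---|
| 2.6% / 1.1% | −1.27 | 2.9% |
| 6.6% / 2.8% | −1.22 | 4.4% |
| 13.1% / 5.5% | −1.11 | 8.7% |

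Check on the last row: the expected value of the reduction over patients below 0 is 1.40 × 0.262 − 2.20 × 0.326 = −0.350 in the test arm, so its per-protocol mean is (1.40 + 0.5 × 0.350)/(1 − 0.131) = 1.81. The same steps give 2.92 for the comparator, and 1.81 − 2.92 = −1.11.

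**Case 3: other patterns.** Equal rates (5% / 5% or 10% / 10%) leave the difference at about −1.30 and the error at about 2.5%. With 5% rescued in the comparator only, the difference is −1.54 and the error 0.4%, a bias against non-inferiority.

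**Does mITT remove it?** Not if T10 scores after rescue are used as observed. With 13.1% / 5.5% rescued, false non-inferiority is 5.6% if rescue adds 1.5 NRS points to the reduction and 12% if it adds 3 (both gains assumed).

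**Scoring rescued patients as zero reduction.** Under Case 2 the error becomes 2.8%, 3.6% and 5.5%. It stays somewhat above 2.5% because in this model every rescued patient had worsened, so zero is a lenient score.

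**Power.** For H3 at a true difference of −0.16, power is 93% at 88 per arm and still 91% at 81. The issue is bias, not lost numbers.

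**The case against.** The strongest reply is that the direction is conditional. A reader might infer that the exclusion always favours non-inferiority. It does not, as Case 3 shows. On the plan's expected reductions methoxyflurane is better in H1 (3.77 − 2.54 = +1.23) and in H2 (3.77 − 2.70 = +1.07). If those hold, more comparator failures would be dropped and the tests would be harder. Only H3 expects a slightly worse test arm (2.54 − 2.70 = −0.16). This stands and limits the point. It does not remove it, because the error rate must hold when the test arm is worse by the margin.

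Early rescue may also be rare. Rescue for failure follows repeated doses, and "The patient may receive additional doses of IMP from 5 min after first dose", which leaves about five minutes. Not every excluded patient need be a failure, since rescue is any other analgesic and Table 4 foresees procedure-related rescue. Many poor responders will still be under titration at T10 and stay in the set. At 1–3% rescued under a common rule the effect is small. This stands too.

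A reader might take mITT to be a mere sensitivity check. The wording, "confirmed, for sensitivity reasons, on the modified intention to treat population", can equally mean that both sets must agree, and the full protocol may settle it. The article's decision chain does not.

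A reader might also infer that morphine patients with failed cannulation are dropped in large numbers, because the Background says "cannulation has been described to fail in 12–26% of adults". That is background literature, not a rate expected in this trial. Table 3 places access attempts before T0, and the article does not say that such patients count as rescued. Morphine is only ever the comparator, so dropping its failures would work against non-inferiority in H2 and H3.

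**Conclusion.** The point holds in conditional form. The deciding population is selected on a post-randomisation outcome, in a trial that says it compares regimens. The selection can favour non-inferiority when early rescue is commoner in the test arm, as a common rescue rule would produce if that regimen is truly worse.

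The size rests on assumed rescue rates, normally distributed reductions with SD 2.20, 90 per arm and the 95% CI rule. At the margin, false non-inferiority goes from 2.5% to about 3–9% with 3–13% of the test arm rescued under a common rule, and to about 5–27% with 2–10% rescued in the test arm only. The second range is the extreme, since it needs no early rescue at all in the comparator, and it should not be read as a forecast.

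Two gaps remain whatever the rate: whether mITT success is required at each step, and how scores after rescue are handled.

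**What to change.** Before the data are examined by arm:

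1. Keep patients who received the allocated drug and were rescued before T10, in both the mITT and the per-protocol set. Score them by one pre-specified failure rule, for example zero reduction from baseline, with the last NRS before rescue as a sensitivity analysis. Name one rule as primary, since the two can give different answers.
2. State that at each step of H1, H2, H3 the lower 95% limit must exceed −1.3 in both sets, so scored, before testing proceeds.
3. Show the set that excludes rescued patients only as a sensitivity analysis, and report early rescue by arm with its reason.
4. Do not extend the zero score to morphine patients who were never dosed because access failed. At the Background rates that would lower the comparator mean by 0.12 × 2.70 = 0.32 to 0.26 × 2.70 = 0.70 points (25–54% of the margin) and make H2 and H3 easier.

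The change is to wording and analysis code. Time and dose of rescue, and NRS at baseline and 5 minutes, are already recorded. The double requirement costs a little power, and the H3 figures above suggest room for it.

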### NRS pain score scale

NRS is a scale with integer values from 0 to 10 where 0 indicates no pain and 10 indicates unbearable pain. Patients indicate on a line with numbers ranging from 0 to 10 or verbally, what numbered value the pain correlates to, and the score is documented in the case report form (CRF).

### Endpoints

Primary endpoint is the change in NRS pain score measured prior to administration of IMP to 10 min after IMP administration; see Table 4 for secondary and exploratory endpoints.

**Table 4 Tab4:** Study endpoints

Primary endpoint	• Changes in pain score from T_0_ to T_10_
Secondary endpoints	• Changes in pain score from T_0_ to T_5_, T_20_, T_30_ and end of mission T_ED_ • Need for additional analgesia not in the regimen of the allocated treatment group • Differences in time arrival to administration of IMP registration of AE and SAE during study period until end of intervention • Time from ambulance personnel arrival to first measure > 2 points reduction in NRS from baseline • Change in level of sedation from T_0_ to T_10_ and T_30_ • Change in RR T_0_ to T_10_ and T_30_ • Change in SBP T_0_ to T_10_ and T_30_ • Likert scale of HCP satisfaction at end of mission • Likert scale of patient satisfaction at end of mission • Registration of AE and SAE during study period until end of intervention
Exploratory endpoints	• Analyze primary and secondary efficacy endpoints stratified by diagnosis or diagnosis groups • Proportion of patient receiving rescue treatment related to procedures (reposition of fractures, relocation, etc.) • Attempts of vascular cannulation access • Change in NRS and time to a significant NRS reduction compared to level of competence • Ambulance personnel competence and patient satisfaction • Analyze primary and secondary efficacy endpoints stratified by level of troponin after ED admission and sign of ACS on ECG at scene • Analyze AE and SAE in relation to concomitant therapy and other non-IMP determinants

*IMP* Investigational medicinal product, *AE* Adverse event, *SAE* Severe adverse event, *NRS* Numeric rating scale, *RR* Respiratory rate, *SBP* Systolic blood pressure, *HCP* Health care personnel, *ED* emergency department, *ACS* Acute coronary syndrome, *ECG* Electrocardiogram, *T*_*-x*_ Scene arrival, *T*_*0*_ Time of IMP administration, *T*_*5*_ 5 min after IMP administration, *T*_*10*_ 10 min after IMP administration, *T*_*20*_ 20 min after IMP administration, *T*_*30*_ 30 min after IMP administration, *T*_*ED*_ Time arrival emergency department or end of service

